## Abstract

**Background:**

Colorectal cancer (CRC) is the third most prevalent type of cancer in the world. Its prognosis is closely related to the disease stage at the time of diagnosis. Early detection of symptomless CRC or precursor lesions through population screening could reduce CRC mortality. However, screening programs are only effective if enough people are willing to participate. This study aims to asses the uptake of a second round of fecal occult blood test (FOBt) based screening and to explore factors that could potentially increase this uptake.

**Methods and design:**

Two years after the first screening round, 10.000 average risk persons, aged 50 to 75, will again receive an invitation to participate in immunohistochemical FOBt (iFOBt) based screening. Eligible persons will be recruited through a city population database. Invitees will be randomized to receive either an iFOBt with a faeces collection paper or an iFOBt without a collection paper. The iFOBts will be analyzed in a specialized laboratory at the Academic Medical Centre. Positive iFOBts will be followed by a consultation at our outpatient clinic and, in the absence of contra-indications and after informed consent, by a colonoscopy. The primary outcome measure is the participation rate. Secondary outcome measures are the effect of the addition of a collection paper on the participation rate, reasons for participation and non-participation, measures of informed choice and psychological consequences of screening and measures of psychological and physical burden associated with the iFOBt and the colonoscopy. Another secondary outcome measure is the diagnostic yield of the program.

**Discussion:**

In order to implement population screening for colorectal cancer in the Netherlands, information is needed on the uptake of repeated rounds of FOBt-based screening and on factors that could potentially increase this uptake in the future since effectiveness of such a program depends on the willingness of persons to participate. This study will provide information on the actual uptake and perception of a second round of iFOBt-based screening. The results of this study will contribute to the future implementation of a national colorectal screening program in the Netherlands.

**Trial registration:**

Dutch Trial register: NTR1327

## Background

Colorectal cancer (CRC) is the third most prevalent type of cancer in the world. Each year more than 940.000 persons are diagnosed with CRC and 500.000 persons die from the disease [1]. In the Netherlands, CRC accounted for over 4700 deaths in 2007[2,3]. The prognosis of patients with CRC is closely related to the disease stage at the time of the diagnosis. Five-year survival is 90% in localized disease but only 68% for disease with lymph node involvement. If distant metastases are present, survival drops to 10%[4]. Many patients are diagnosed in an advanced stage, thus resulting in poor survival. Early detection of symptomless CRC or its precursor lesions by population screening could reduce CRC mortality since removal of these precursors during colonoscopy reduces the incidence of CRC[5].

There are several options for CRC screening falling into two broad categories: stool tests and structural exams. Stool tests include fecal occult blood tests (FOBt) and tests for exfoliated DNA. Structural exams include flexible sigmoidoscopy, total colonoscopy and computed tomographic colonography (CTC). FOBt is the only screening method with a documented CRC mortality reduction in randomized controlled trials. The efficacy of strategies based on repeated guaiac FOBt has been established in three randomized trials and one non-randomized controlled trial [6-9]. A meta-analysis after several rounds of these continuing trials showed a CRC mortality reduction of 14% during a 10-year screening period[10].

The United Kingdom, France, Finland and Australia provide nationally organized bowel cancer screening programs. Several other countries, including Germany, the United States and Italy, recommend CRC screening but do not offer screening as part of an organized national program. In the past few years, several project-groups have started to study the feasibility, acceptance and cost-effectiveness of a national colorectal cancer screening program in the Netherlands. In 2006 our research group, in collaboration with the Radboud Hospital in Nijmegen, started a study on the implementation of invitation based population screening with FOBt in two regions of the Netherlands. In this pilot study, 20.000 asymptomatic individuals, aged 50–75, were invited to take part in one round of FOB testing and they were randomized to either a guaiac-based (gFOBt) or immunochemical FOBt (iFOBt). Invitation of participants was from May 2006 until January 2007. Primary goals of this implementation study were to determine the participation rate, feasibility and logistics of this type of screening. In this study, an overall participation rate of 53% was observed. Participation rate in the iFOBt group was significantly higher than in the gFOBt group (60% vs 47%)[11]. Also, detection rates for advanced adenomas and cancer were higher for iFOBt although also more colonoscopies had to be performed.

Since the effectiveness of a FOBt-based screening program in reducing mortality from CRC is highly dependent on participants' willingness to repeat testing at regular intervals, there is a need for information on adherence to consecutive rounds of FOBt screening. Information on actual uptake is needed before well-informed decisions on nationwide introduction of a CRC screening programme in the Netherlands can be made.

To obtain information on participants' willingness to take part in repeated rounds of FOBt-based screening we decided to add a second screening round to the pilot study described above. In the present study the same cohort of the Amsterdam region that was studied in the first screening round will be again invited for FOBt-based screening after an interval of two years. Only the iFOBt will be used in this second round since it was associated with a higher participation rate in our first round and it had higher CRC detection rates. By focusing on the exact same group of persons we intend to represent the real life situation once a nationwide program is in place.

Participation rate will be the major focus of the present study but we will also try to identify factors that are associated with participation and non-participation. Particularly, we want to explore whether the addition of a collection paper makes people more willing to participate. It is hypothesized that the handling of faeces is a barrier to participation. Facilitating the collection process by adding a collection paper could potentially lower this barrier and increase participation.

Besides pursuing a high participation rate, it is also important that invitees are enabled to make a well-informed decision on participation. In order to make an informed decision invitees need to have sufficient insight into the pros and cons of taking part in the program. This study will therefore also evaluate to what extent invitees' decisions to participate or not are made in a well-informed fashion. Furthermore, the psychological and physical impact of taking part in the screening program and possible follow-up investigations will be evaluated. Insight into the impact of participation is important because negative experiences can act as a barrier for future participation. Finally, the diagnostic yield of this second round of screening will be evaluated and compared to the first round. It is hypothesized that the majority of advanced lesions were already detected during the first round. Therefore we expect to find a smaller number of patients with advanced lesions compared to the first round.

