#### Secondary objectives

• To evaluate the effect of the addition of a faeces collection paper to the iFOBt-kit on the participation rate;

• To compare participation rates between the first and second round;

• To compare the participation rates in groups that were defined as participants or non-participants in the first round;

• To evaluate the diagnostic yield (detection rates of cancer, high-risk adenoma and low-risk adenoma) and complication rate of iFOBt and colonoscopy and to compare these to results of the first screening round;

• To compare the baseline characteristics of participants and non-participants;

• To evaluate factors influencing the decision to participate;

• To evaluate invitees' ability to make a well-informed decision to participate;

• To evaluate participants' experience with the screening program in terms of their perception and the burden of the iFOBt;

• To evaluate the psychological impact on participants of receiving a positive test result;

• To evaluate the burden of the colonoscopy in iFOBt positives;

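### The hypothesis that round 1 already found most advanced lesions is plausible only for round 1 responders, and a yield comparison not split by round 1 test and response cannot show it

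*Protocol article*

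**What the plan says.** The Background hypothesises: "It is hypothesized that the majority of advanced lesions were already detected during the first round". The next sentence draws the expectation of fewer patients with advanced lesions than in round 1. Neither sentence is limited to round 1 responders.

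On round 1, the Background reports that invitees in two regions were randomised to gFOBt or iFOBt, that "an overall participation rate of 53% was observed" (60% with iFOBt, 47% with gFOBt), and that "detection rates for advanced adenomas and cancer were higher for iFOBt". On round 2 it says: "Only the iFOBt will be used in this second round".

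Study population lists three groups among the round 2 invitees: non-responders, responders and first-time invitees. Round 1 positives who had a colonoscopy are not re-invited.

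Secondary objectives defines diagnostic yield as detection rates of cancer, high-risk adenoma and low-risk adenoma. The aim is to evaluate the yield "and complication rate of iFOBt and colonoscopy and to compare these to results of the first screening round". Data analysis names the three groups for participation rates only. No section splits any group by the test offered in round 1.

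**The concern.** Lesions in people who were not tested cannot have been found by the programme, and nearly half of the round 1 invitees were not tested. A statement that most lesions were already found therefore conflicts with the reported participation unless almost every lesion in participants was detected.

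The comparison meant to bear on it also changes several things at once. Round 1 used two tests and round 2 uses one. Everyone in round 1 was at the first round of the pilot, whereas round 2 mixes people never screened in it, people whose earlier screen was gFOBt, and people on a second iFOBt. Those found positive and examined have left.

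What is at stake is the repeat-screen yield of iFOBt, which a national programme would need. A pooled figure could fall without most lesions having been found earlier. It could also stay level or rise although yield in re-screened people has dropped.

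**Working it through.** **Inputs from the protocol article (Background).** Round 1 participation: iFOBt 0.60, gFOBt 0.47, overall 0.53. **Assumptions.** 1:1 allocation (the ratio is not stated); equal lesion prevalence in participants and non-participants. The article gives no sensitivity and no colonoscopy uptake, so S_i and S_g below (share of lesions found per iFOBt and per gFOBt participant, including colonoscopy uptake) are assumed ranges.

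**1. The plan's own figure.** 0.5 × 0.60 + 0.5 × 0.47 = 0.300 + 0.235 = 0.535, which agrees with the reported 53% and so with 1:1 allocation.

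**2. Ceiling and requirement, whole cohort.** Share found = 0.300 × S_i + 0.235 × S_g.
- Perfect tests and full colonoscopy uptake: 53.5% (53% on the reported overall rate).
- Average detection needed for one half: 0.50/0.535 = 93.5%, or 0.50/0.53 = 94.3%.
- With S_i = 100%, S_g must still exceed (0.50 − 0.300)/0.235 = 85%.

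**3. Share found over assumed detection.** The responder column divides by 0.535.

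| S_i / S_g | Whole cohort | Round 1 responders only |
|---|---|---|
| 0.5 / 0.3 | 22% | 41% |
| 0.7 / 0.5 | 33% | 61% |
| 0.9 / 0.7 | 43% | 81% |
| 0.9 / 0.9 | 48% | 90% |
| 1.0 / 0.9 | 51% | 96% |

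**4. Who is screened in round 2.** Cohort weights are 0.300 iFOBt responders, 0.235 gFOBt responders and 0.465 non-responders. Assume 85% repeat uptake in responders.
- Non-responder uptake 15%: share with an earlier iFOBt = 0.255/(0.255 + 0.200 + 0.070) = 49%.
- Non-responder uptake 30%: 0.255/(0.255 + 0.200 + 0.140) = 43%.
- Uptake of 50% in every group: 30%.

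First-time invitees and the removal of examined positives lower these shares further.

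**5. Can the comparison show earlier detection?** Two illustrations follow. All inputs are assumed: misses independent between rounds, no new lesions, no first-time invitees, denominators not reduced for removed positives. Prevalence p cancels in the ratios.

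*A: S_i 0.70, S_g 0.40; uptake 80% (responders), 25% (non-responders).*
- Round 1 finds 0.210 + 0.094 = 0.304 of the lesions, so the majority hypothesis is false.
- Round 2 finds 0.300×0.30×0.80×0.70 + 0.235×0.60×0.80×0.70 + 0.465×0.25×0.70 = 0.050 + 0.079 + 0.081 = 0.211.
- Count ratio 0.211/0.304 = 0.69, so the predicted fall occurs anyway. Only 0.050/0.211 = 24% of round 2 lesions come from a repeat iFOBt.
- Per person screened, pooled: (0.211/0.544)/(0.304/0.535) = 0.387/0.568 = 0.68. Repeat iFOBt against first iFOBt: (0.30×0.70)/0.70 = 0.30.

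*B: S_i 0.30, S_g 0.15; uptake 85% and 30%.*
- Round 1 finds 0.090 + 0.035 = 0.125.
- Round 2 finds 0.300×0.70×0.85×0.30 + 0.235×0.85×0.85×0.30 + 0.465×0.30×0.30 = 0.054 + 0.051 + 0.042 = 0.146.
- Count ratio 0.146/0.125 = 1.17. Per person screened, pooled: (0.146/0.594)/(0.125/0.535) = 0.246/0.234 = 1.05. Repeat against first iFOBt: (0.70×0.30)/0.30 = 0.70.

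In A the pooled rate falls by about a third where the like-for-like rate falls by 70%. In B the pooled rate rises slightly while the like-for-like rate falls by 30%.

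**The case against.** A reader might infer that the hypothesis cannot be true for this cohort. The documents do not support that. The ceiling of 53 to 53.5% lies just above one half, and excluding a majority needs a limit on sensitivity that the article does not give. The participation rates pool two regions, whereas round 2 re-invites only the Amsterdam cohort, for which no separate rate is given; so close to one half, a few points matter. If the sentence was meant for people screened in round 1, it can well hold. What remains is that the text does not say so.

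The greater sensitivity of iFOBt is also an inference. The article reports higher detection rates without a denominator; per invitee, uptake of 60% against 47% would raise the iFOBt rate by itself. The ceiling in step 2 does not depend on this.

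Nor does the article say that the groups will be pooled for yield, and stratification of a secondary outcome may stand in a fuller document. That is fair, but the hypothesis, the inference and the comparator are all stated here, and followed as written they do not support the conclusion. The groups that are named do not include the round 1 test, so they would not separate gFOBt from iFOBt responders.

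Overall round 2 yield is a legitimate programme figure, and Secondary objectives already defines yield as rates; patient numbers appear only in the Background expectation. Finally, a reader might suspect a change of haemoglobin cut-off between rounds. The iFOBt section says the same test was used and gives 50 ng/mL; nothing indicates a different round 1 threshold.

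**Conclusion.** The point stands in a limited form. For the whole invited cohort the hypothesis is implausible, not impossible: it needs about 94% detection per participant, and at assumed detection of 50 to 90% (iFOBt) and 30 to 70% (gFOBt) round 1 would have found about 22 to 43% of lesions. This rests on the pooled two-region rates, 1:1 allocation and equal prevalence in non-participants. For round 1 responders it is plausible.

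The comparison with round 1, as stated, confounds earlier detection with test type, screening history and who takes part. Neither a fall nor a rise in yield, or in patient numbers, can be attributed to earlier detection. This part follows from the design and needs no assumed sensitivity; the illustrations only show that the error can go either way.

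This should be fixed. It is not critical, because the primary objective is participation, the sample size rests on participation alone, and no decision rule depends on the hypothesis.

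**What to change.** - Limit the hypothesis in the Background to round 1 responders, and state the expectation as a detection rate instead of a number of patients.
- Make the main yield comparison the detection rate per person screened in round 1 iFOBt-negative participants re-screened in round 2, against the first screen in the round 1 iFOBt arm.
- Report former gFOBt participants, former non-responders and first-time invitees separately.
- Keep the overall round 2 yield as a descriptive programme figure.

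This changes wording and analysis grouping only. It needs linkage of each round 2 participant to the round 1 test and result, and no additional participants. The price is fewer lesions in the main contrast and a wider interval.

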## Methods and design

### Objectives

#### Primary objective

To evaluate the participation rate in a second round of iFOBt-based colorectal cancer screening in the Netherlands, two years after the first round.

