### Data analysis

The primary goal of this second FOBt-based screening round is to assess the overall participation rate and to compare participation rates between groups (participants (1) and non-participants (2) to the first round and new invitees (3), within all three groups invitees will be randomized to receive a collection paper or not).

Group differences will be calculated using the Chi-square test. Descriptive statistics will be used to compare baseline characteristics of the subgroups.

To assess the effect of baseline characteristics and independent variables (assessed in the questionnaires) on the participation rate, multivariate analysis will be performed.

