## Discussion

This study will provide information on the uptake of a colorectal cancer screening program using repeated immunochemical FOBt in the Netherlands. These data are crucial since reliable and precise data on the degree to which people are willing to participate in a second round of screening in the Netherlands are lacking and the effectiveness of a screening program is directly influenced by the participation rate. Insight into factors that are related to participation in biannual screening can be used to optimize future screening programs. If this study shows that a less burdensome faeces collection procedure by the use of a collection paper has a positive effect on the participation rate, this information is useful for a future population screening program. Furthermore, we can anticipate on the psychological and physical burden of participating in a screening program based on participant's experiences in the present study. In a future screening program this burden should be reduced to a minimum to ensure a high participation rate.

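### The overall round 2 rate mixes people previously offered gFOBt, people previously offered iFOBt and new invitees, so it does not directly estimate uptake under repeated iFOBt screening

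*Protocol article*

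**What the plan says.** The primary objective is "To evaluate the participation rate in a second round of iFOBt-based colorectal cancer screening in the Netherlands, two years after the first round". The Background explains that "the same cohort of the Amsterdam region that was studied in the first screening round will be again invited for FOBt-based screening", this time with iFOBt for everyone, and gives the purpose: "By focusing on the exact same group of persons we intend to represent the real life situation once a nationwide program is in place". The Discussion is more specific about the test: "This study will provide information on the uptake of a colorectal cancer screening program using repeated immunochemical FOBt in the Netherlands".

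The Background also reports that round 1 was randomised between gFOBt and iFOBt. Uptake was 47% with gFOBt and 60% with iFOBt, and "an overall participation rate of 53% was observed".

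The Data analysis section states: "The primary goal of this second FOBt-based screening round is to assess the overall participation rate and to compare participation rates between groups". The groups are round 1 participants, round 1 non-participants and new invitees. The multivariate model takes baseline characteristics and variables from the questionnaires. The Sample size section plans one overall rate in 10,000 persons with a 95% confidence interval of plus or minus 1%. The round 1 test appears in none of these.

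**The concern.** For people in the former gFOBt arm, round 2 is a first offer of iFOBt, made after a test with lower uptake. A programme that used iFOBt from the start would contain nobody with that history. New invitees are not in a second round at all, yet they count in the overall rate. The planned figure is therefore an average over three invitation histories, and only one of them matches repeated iFOBt.

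Two results are affected. The first is the Discussion's statement about repeated immunochemical testing, which the pooled rate supports only if the histories happen to give similar uptake. The second is the comparison of round 1 responders with non-responders. The non-responders include a disproportionate number of people who declined gFOBt and had never been offered iFOBt, so the contrast combines willingness to be screened with the test previously offered.

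**Working it through.** **The plan's own margin.** 1.96 × √(0.5 × 0.5 / 10,000) = 0.98 points. The stated 1% reproduces.

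**Share offered gFOBt in round 1.** The allocation ratio is not stated. Let w be the gFOBt share. Then 60(1 − w) + 47w = 53, so w = 7/13 = 54%, or 46% to 62% allowing for rounding of the three rates. About half is a fair reading. These rates cover both regions of the pilot, not Amsterdam alone. The steps below use w = 0.5.

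**Difference between the iFOBt-iFOBt rate and the pooled rate, re-invited persons only.** Let r be round 2 uptake in round 1 responders. Let n be uptake in iFOBt non-responders and n_g uptake in gFOBt non-responders.

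- Former iFOBt arm: 0.60r + 0.40n
- Former gFOBt arm: 0.47r + 0.53n_g
- Difference from the pool: 0.5 × (first − second)

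The documents give no value for r, n or n_g. All values below are assumptions.

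| r | n | n_g | iFOBt arm | gFOBt arm | Difference (points) |
|---|---|---|---|---|---|
| 1.00 | 0 | 0 | 60.0% | 47.0% | 6.5 |
| 0.85 | 0.20 | 0.20 | 59.0% | 50.6% | 4.2 |
| 0.80 | 0.30 | 0.30 | 60.0% | 53.5% | 3.3 |
| 0.70 | 0.40 | 0.40 | 58.0% | 54.1% | 2.0 |
| 0.85 | 0.20 | 0.30 | 59.0% | 55.9% | 1.6 |
| 0.85 | 0.20 | 0.36 | 59.0% | 59.0% | about 0 |

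With n_g = n the difference is 0.065 × (r − n). At w = 0.54 the first row becomes 0.54 × 13 = 7.0.

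**Why zero is plausible.** Suppose everyone who accepts gFOBt would also accept iFOBt. Then 60 − 47 = 13 of the 53 points of gFOBt non-response (25%) are people who would have taken iFOBt. If they behave like responders once offered it, the gFOBt arm's rate is 0.47r + 0.13r + 0.40n = 0.60r + 0.40n. That equals the iFOBt arm's rate for every r and n. In the last row, n_g = (0.13 × 0.85 + 0.40 × 0.20)/0.53 = 0.36. If n_g were higher still, the sign would reverse.

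**Composition of the response groups at 1:1 allocation.** gFOBt share of non-responders: 0.53/(0.53 + 0.40) = 57%. gFOBt share of responders: 0.47/(0.47 + 0.60) = 44%.

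**Margin for the iFOBt-iFOBt stratum at 50%.** 1.96 × √(0.25/5,000) = 1.386 points; 1.96 × √(0.25/4,000) = 1.549 points.

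**Not in these figures.** New invitees dilute the gFOBt share of the overall rate, but their number is not given. Under Study population, round 1 positives who had a follow-up colonoscopy are not re-invited. The Background says iFOBt led to more colonoscopies, so more responders leave the former iFOBt arm, which would narrow the difference when responders have the higher uptake.

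**The case against.** The strongest reply concerns the target. The Abstract, the Background, Study design and Data analysis mostly speak of a second round of FOBt-based screening, and the change to iFOBt is disclosed. The primary objective can be read as a second round in which iFOBt is the test used. On that reading the overall rate answers it. This stands. The narrower target rests mainly on the Discussion sentence, helped by the stated wish to mirror a national programme.

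A reader might infer that the overall rate falls below the repeated-iFOBt rate by several times the 1% margin, and that the two agree only if round 1 behaviour does not predict round 2. The documents do not support this. It requires non-responders in both arms to have the same round 2 uptake, although one group declined a test with lower uptake and had not yet been offered the other. The zero case above has round 1 behaviour predicting round 2 strongly and still gives no difference.

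The 1% is also a statement of sampling error and claims nothing about a programme that started with iFOBt. That is correct.

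Finally, an article may leave strata and covariates to a fuller document, and nothing here forbids a split by round 1 test. This limits the weight of the point. It does not remove it, because the article itself names the history groups and makes the repeated-iFOBt statement.

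**Conclusion.** The point holds as a mismatch between the planned summary and one of the conclusions to be drawn from it. It does not show that the primary rate is wrong. The overall rate is a valid description of this cohort, with a correct sampling margin. It is not a direct estimate of uptake under repeated iFOBt.

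Among re-invited persons the difference could run from about 0 to about 6.5 points, before allowing for new invitees and for round 1 positives who are not re-invited. The upper end needs full persistence of round 1 behaviour. The lower end needs only that people who declined gFOBt but would take iFOBt behave like responders. Neither size nor direction can be settled from the documents. The 1:1 allocation is inferred and the round 1 rates come from both regions. The imbalance in the response groups (57% against 44% from the gFOBt arm) rests on the same two assumptions but not on any round 2 uptake.

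Because the difference is unknown and the round 1 test was randomised, it is better measured than assumed. This is a worthwhile, inexpensive improvement.

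**What to change.** - **Data analysis:** keep the overall rate as the description of the cohort. Add round 2 participation by round 1 test offered (iFOBt, gFOBt, none), overall and, for re-invited persons, separately in round 1 responders and non-responders. Include round 1 test in the multivariate model of participation.
- **Sample size:** state the margin for persons offered iFOBt in both rounds, about ±1.4 to 1.5 points at 50% for an assumed 5,000 to 4,000 persons. Replace the assumed count with the actual one.
- **Discussion:** base the statement on repeated immunochemical testing on that stratum, and describe the overall rate as the uptake of this mixed cohort.

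The cost is analysis wording and a somewhat wider margin for the repeated-iFOBt estimate. The round 1 allocation should already be on record from the first trial, so no further invitations or data collection are needed.
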